#### Data collection methods

The PI will maintain up-to-date records that cover point 1 in the “Outcome measures” section. Feedback from members of the research team, participating licenced premises and participants will be obtained and recorded throughout the study.

Electronic datasets will be created in Excel to monitor:Licenced premises that are approached by the PILandlords/managers who express willingness to participateLandlords/managers who sign a letter of accessParticipants who consent to participate (and at each separate participating licenced premises)Participants who consent and do not complete two study sessionsParticipants who consent and drop out during or after the intervention study sessionParticipants who consent and drop out during or after the control study session

To track the number of study-specific drinks served, the RA will stamp the participant’s randomisation card each time they are supplied with a fresh drink. The randomisation card will be handed to the PI at the end of each study session.

Participants will be briefed that if they do not consume the entirety of a study-specific drink they should return their drinking vessel to the RA. The RA will alert the PI who will measure the amount of alcohol that has been left in the vessel. The PI will quantify, in UK units, the amount of alcohol that each participant has left throughout each study session and deduct this from the number of UK units of alcohol served to each participant, which will be calculated by the PI. The number of UK units of alcohol will be converted to, and additionally displayed as, grams of alcohol for an international audience.

The PI will also record the times at which each participant commences and concludes each of their study sessions. This will enable a comparison between the duration of participants’ study sessions under each of the study conditions, which will indicate whether participants may be concluding their study sessions and then consuming non-study drinks.

#### Collecting data from deviant participants

Participants who are seen by the PI, the RA or the BP to be obviously and persistently breaching the protocol will be removed from the study, and their data will not be utilised. Similarly, if a participant wishes to discontinue in the pilot trial during a study session, no further data will be collected.

### Data analysis

The efficacy and efficiency of the study processes and the rates of licenced premises recruitment, participant recruitment and attrition will be analysed and reported using descriptive statistics.

Mean value and 95% confidence intervals will be used to compare the number of UK units of alcohol consumed and the mean duration of participation in study sessions, between the intervention arm and the control arm.

The mean and SD of the number of UK units of alcohol consumed will be used to calculate a sample size for future, larger scale studies. The components of the sample size calculation will be delta (mean difference/SD of mean difference) = derived from a calculation of the data, alpha (sig.level) = 0.05, beta (power) = 0.8.

A *t* test, between the sequences AB and BA, will be undertaken to test for a period effect.

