### Outcome measures

The primary outcome is the feasibility of a RCT. A RCT would be deemed feasible if it adheres to the following points:Components of the study protocol are efficient and work together or can be amended to be or do so. These include:The administration of data collection toolsThe consent processThe randomisation processData management processesThe roles and requirements of study personnelThe licenced premise recruitment rate is a minimum of one per month for a minimum of 4 months or until four licenced premises have been recruited.Participant recruitment rate is a minimum of four per study session.The rate of attrition for the pilot trial is less than or equal to 30%, and this does not vary by more than 10% according to the arm of the trial.The sample size is achievable to obtain within a year based on the recruitment rate of licenced premises and participants.

In addition, one participant-centred outcome will be assessed:Whether estimations of the mean and 95% confidence intervals of the number of UK units of alcohol consumed by participants in a single drinking occasion, when they consume BL and B, suggest that people consume fewer UK units of alcohol when they consume reduced strength lager.

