### Sample size

As there are no data from previous studies on which to base a statistical calculation, and there is no consensus in the literature about the required sample size for pilot trials, the sample size has been calculated using preliminary datasets. These preliminary datasets are based on the hypothesis that there is no significant difference between the number of alcoholic drinks individuals consume, regardless of their ABV, which has been shown in a previous study [24].

Firstly, preliminary datasets were created for 40 patrons at each of four different licenced premises with different demographics, based on their average patron’s characteristics, i.e. age and gender. The mean patrons’ age was calculated from each licenced premises’ preliminary dataset. Mean age was used to estimate the number of units that each of the 40 hypothetical patrons would consume under normal conditions, based on age-related population data for alcohol consumption [29]. The estimated number of units consumed under normal conditions was reduced by 27% to give the estimated number of units consumed under the intervention: the difference in ABV between BL and B is − 27%. Estimated mean units and SD for units consumed from BL and B were calculated; a conservative estimate for SD in the intervention arm was used: the same SD as in the control arm. Where the licenced premises’ population incorporated a higher proportion of male to female consumers, this was accounted for in the calculations and the mean consumption increased accordingly. From these data, the estimated mean difference and SD of the mean difference of UK units of alcohol consumed were calculated. These data enabled delta to be calculated, 0.3977.

Preliminary data for the licenced premises with the largest SD was used to calculate the sample size using the Rstudio software ‘R Stats Package’ and the function power.t.test [30]: this provided the most conservative calculation of sample size. The figures that were inputted into Rstudio were alpha = 0.05, beta (power) = 0.8, delta = 0.3977, SD = 1. The sample size for a two-sided paired *t* test was calculated as 52: 52 participants participating in two trial arms. As this does not account for attrition, participants who drop out of the pilot trial will be replaced.

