## Discussion

The aim of this pilot trial is to assess the feasibility of a RCT to assess the effect of alcohol strength on alcohol consumption in a single drinking occasion within licenced premises; to our knowledge, no trials to date have investigated this. If the pilot trial is successful, a larger scale RCT could be undertaken, which would test an intervention that has the potential to improve public health by reducing alcohol consumption.

The pilot trial is of a cross-over design, which has the advantages of eliminating between participant variation, and being more economic due to a smaller sample. Whilst there is no risk of a carryover effect, the main disadvantage of using a cross-over design in this study is the potential for a period effect. This will be tested for during data analysis and, if present, subsequently reported.

Whilst one of the main advantages of this study is its naturalistic design, due to the complexity of undertaking research within licenced premises, some compromises have been necessary. For example, ideally the intervention and control lagers would be supplied from “tapped” barrels to align with how the majority of lager is sold to customers within licenced premises. As this is not feasible for a small-scale study, lager will be supplied from duct-taped cans. Although this reduces the face validity of the study, other measures have been put in place to improve the study’s face validity. For instance, lager will not be sold by the can but poured from multiple cans into a pint glass so that a full pint is served.

There are some associated challenges that may be encountered during the pilot trial. These include recruiting licenced premises, retention of participants across two study sessions and participant adherence to the study protocol. Processes that have been put in place to minimise these challenges are discussed below.

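### The trial is sized on a paired difference, but the comparison of units is described as means and 95% CIs by arm and never names that difference as the estimate

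*Protocol article*

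**What the plan says.** **Sizing.** The Sample size section reports that "the estimated mean difference and SD of the mean difference of UK units of alcohol consumed were calculated". It then enters "alpha = 0.05, beta (power) = 0.8, delta = 0.3977, SD = 1" into R, using "the function power.t.test", for a two-sided paired t test. The result is given as "52 participants participating in two trial arms". The SD in the intervention condition is taken as equal to that in the control condition. Participants who drop out are replaced.

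**Comparison.** The Outcome measures section makes the participant-centred outcome depend on whether "estimations of the mean and 95% confidence intervals of the number of UK units of alcohol consumed by participants in a single drinking occasion", on Bud Light and on Becks, suggest lower consumption with the weaker lager. Aim/objectives words the objective in much the same way. Under Data analysis, "Mean value and 95% confidence intervals will be used to compare the number of UK units of alcohol consumed" between the intervention and control arms, and session duration is treated in the same sentence.

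**Paired quantity.** The ratio of the mean difference to its SD does appear under Data analysis, but only as an input to the sample size of a later trial. The one t test named there is for a period effect.

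**Rationale for the design.** The Discussion credits the cross-over with "eliminating between participant variation, and being more economic due to a smaller sample".

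**The concern.** The sample size and the stated comparison do not describe the same estimate. The 52 is right for a paired difference. The outcome and analysis text describes a mean and interval for each product, set against each other. The width of such an interval comes from the spread between people, which is the component the Discussion says the design eliminates.

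An analyst who followed the text as it most naturally reads could report two wide, overlapping intervals and conclude that the hypothesis is not supported, while the paired difference from the same data shows a clear reduction. Overlap of two 95% CIs does not show absence of a difference, and it is least informative when the same people supply both means. No rule says what pattern of intervals would count as support.

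Session duration is described in the same way. Under Data collection methods it is the indicator of whether participants may be ending sessions early and then drinking elsewhere, so an imprecise comparison could hide that.

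**Working it through.** **Inputs.** From the Sample size section: two-sided alpha 0.05, power 0.8, standardised paired difference 0.3977 (SD 1), n = 52, equal SDs in the two conditions. Not in the article: the within-person correlation ρ between the two sessions. I assume 0, 0.3, 0.5 and 0.7 to show the range.

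**Step 1: reproduce the plan's figure.** For a paired t test the noncentrality is 0.3977 × √n. At n = 52 it is 0.3977 × 7.211 = 2.868 on 51 df, which gives power 0.803. At n = 51 the power is 0.795. The smallest n that reaches 0.80 is therefore 52, as stated. The normal approximation, (1.960 + 0.842)² / 0.3977² = 49.6, is a little lower because it ignores the t correction.

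**Step 2: hold the planned paired effect fixed and vary ρ.** Set the SD in each condition to 1. Then SD of the difference = √(2(1 − ρ)), and true mean difference = 0.3977 × √(2(1 − ρ)).

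**Step 3: width of the interval for the difference, n = 52.**
- Paired: half-width = 2.008 × √(2(1 − ρ)/52), which narrows as ρ rises.
- Unpaired: half-width = 1.983 × √(2/52) = 0.389 whatever ρ is.
- Two separate arm intervals fail to overlap only if the means differ by more than 2 × 2.008/√52 = 0.557, again whatever ρ is.

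| ρ | True difference (arm SDs) | Paired half-width | Unpaired half-width | Non-overlap threshold |
|---|---|---|---|---|
| 0 | 0.562 | 0.394 | 0.389 | 0.557 |
| 0.3 | 0.471 | 0.329 | 0.389 | 0.557 |
| 0.5 | 0.398 | 0.278 | 0.389 | 0.557 |
| 0.7 | 0.308 | 0.216 | 0.389 | 0.557 |

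**Step 4: chance of detecting the planned effect.** The nominal unpaired column uses the standard two-sample formula (noncentral t, 102 df, 52 per condition). The other columns are simulated with normal correlated pairs, 100,000 trials per value of ρ.

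| ρ | Paired CI excludes 0 | Unpaired CI, nominal | Unpaired CI, simulated | Arm CIs do not overlap |
|---|---|---|---|---|
| 0 | 80% | 81% | 81% | 52% |
| 0.3 | 80% | 66% | 69% | 31% |
| 0.5 | 80% | 52% | 53% | 14% |
| 0.7 | 80% | 34% | 24% | 2% |

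The nominal and simulated unpaired figures differ when ρ > 0 because the two-sample formula treats the samples as independent. Either way the power falls as ρ rises. At ρ = 0.5 the two-sample formula would need 101 per condition for 80%.

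The last column applies only if the intervals were judged by overlap, a rule the article does not state.

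**The case against.** The case against has four parts.

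- **The wording leaves room for a paired interval.** Using a mean and 95% CI to compare arms can cover the mean within-person difference. The same section computes that difference and its SD for the future trial, and the Discussion's rationale points to a paired intent. This stands. A reader might infer that the plan discards the pairing, but no sentence says so.
- **No overlap rule is written down.** The objective and outcome ask whether the estimates support or suggest lower consumption. This also stands, so the overlap figures are a warning about one possible reading and not the power of the plan.
- **The loss is not general.** A reader might infer that the stated comparison cannot reach 80%. The article does not support that: a paired CI reaches it, and an unpaired CI does too if ρ is 0. But at ρ = 0 pairing brings no gain, and the Discussion's argument for a smaller sample would fall away.
- **This is a pilot, and the article is condensed.** Feasibility is the primary outcome, the comparison of units is an additional one, no efficacy test is declared, and a fuller analysis plan may name the estimator. This limits the weight of the point. It does not remove it. The article states its comparison in several sections, each time without the paired difference, and uses that difference only for planning a later trial. That is a mismatch in what is stated, not just a detail left out.

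The feasibility criterion on an achievable future sample size is unaffected, because it already uses the mean difference and its SD.

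**Conclusion.** The point holds in a limited form. The 52 is correct for a paired t test. The comparison of units, as most naturally read, is not that analysis and need not deliver the planned power. If the difference were taken with an unpaired CI, nominal power would be about 81% at ρ = 0, 66% at 0.3, 52% at 0.5 and 34% at 0.7. If arm intervals were judged by non-overlap, the figures would be about 52%, 31%, 14% and 2%. These rest on normal data, equal SDs, 52 completers, the planned paired effect and a correlation the article does not give.

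The 80% is the basis on which the number of participants was chosen; the article attaches it to no declared test of effect. It would also be too strong to say that a true effect would usually look unsupported, since that depends on the unstated correlation and on an unstated rule for reading the intervals. As the outcome is additional to feasibility, this is a should-fix.

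**What to change.** In Outcome measures and Data analysis, and to match in Aim/objectives, state:

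- The comparison is the mean within-participant difference (Bud Light minus Becks) in UK units with its paired 95% CI.
- The hypothesis is taken as supported if that CI lies wholly below 0.
- Means and intervals for each product are descriptive only.

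For session duration, report the same paired difference and 95% CI without any power claim, since the trial was not sized on it.

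The cost is wording. The data collected and the 52 participants do not change, and the units comparison then has the 0.803 power on which the 52 was based.

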### Monitoring

#### Safety/harms

There is no reason to believe that this study will lead to an excessive number of adverse events. Although participants will be consuming alcohol, they will be briefed to consume alcohol in their normal manner and processes have been put in place to safeguard against study-related harms. Any adverse events that are reported to the PI will be logged using an adverse event form and reported to the CI and the UREC Chairperson. It will be the UREC Chairperson’s decision whether to terminate the study should the number of adverse events reach a level beyond which would be deemed unacceptable.

#### Data handling, record keeping and retention

Relevant information from electronic correspondence with participants will be encrypted and saved in password-protected folders on an Oxford Brookes University (OBU) computer’s hard drive and deleted from the email account. All hard correspondence will be stored in a locked filing cabinet within a lockable room at OBU.

All hard data collected at the study sites will be securely transferred to locked filing cabinets within a lockable room at OBU at the first available opportunity following each study session. Prior to this, it will be stored in locked cabinet drawers at the PI’s residence. Identifiable and non-identifiable information will be transferred and stored separately.

Qualtrics [34] will host the eligibility surveys, with whom OBU’s Faculty of Health and Life Sciences hold an agreement. Identifiable data from the eligibility surveys will be stored in encrypted and password-protected Excel spreadsheets on an OBU computer’s hard drive.

If a participant withdraws from the study, then all of their information will be destroyed.

Datasets will be kept in accordance with the General Data Protection Regulation (GDPR) [35] and OBU’s Research Data Management Policy [33]. The latter states that study data will be offered and assessed for deposit and retention in a University repository, such as the Research Archive and Digital Asset Repository (RADAR). Data on RADAR will be kept for a minimum of 10 years.

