#### Trial withdrawal

Participants who wish to withdraw from the study will be directed to contact the PI via email or telephone or express this to the PI verbally during a study session.

Participants who are seen by the PI, the RA or the BP to be obviously and persistently breaching the protocol will be withdrawn from the study. These breaches include consuming any alcohol other than the study-specific lager which they have purchased, supplying non-participants with study-specific drinks, and disposing of any study-specific lager without declaring it.

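### The rule to destroy all information on participants who withdraw conflicts with the drop-out records that the attrition criterion needs, and applied literally it biases measured attrition downwards

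*Protocol article*

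**What the plan says.** Four parts of the protocol article bear on what happens to the data of someone who leaves.

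- **Data handling, record keeping and retention:** "If a participant withdraws from the study, then all of their information will be destroyed". No exception is stated.
- **Data collection methods:** Excel datasets are to track those who consent, those who consent but do not complete both sessions, and those who drop out in or following the intervention session and the control session, separately.
- **Collecting data from deviant participants:** persistent breachers "will be removed from the study, and their data will not be utilised". For others, "if a participant wishes to discontinue in the pilot trial during a study session, no further data will be collected".
- **Trial withdrawal:** participants withdraw by telling the principal investigator. Those seen "to be obviously and persistently breaching the protocol will be withdrawn from the study".

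Outcome measures states "The primary outcome is the feasibility of a RCT". One of its conditions is attrition of at most 30%, provided that "this does not vary by more than 10% according to the arm of the trial". Data analysis commits to reporting attrition descriptively. Sample size says that drop-outs will be replaced.

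**The concern.** Attrition is one of the pre-set conditions for calling a definitive trial feasible. It can be measured only if those who leave stay visible in the numerator and the denominator. One section orders the records that make them visible; another orders everything held on withdrawn participants to be destroyed. A team following both as written cannot comply.

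The loss is not neutral. Removing a non-completer from both counts always lowers the rate, so any error in the overall figure favours a pass. Replacement adds to this, because the surviving file drifts towards 52 completers.

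The split by arm is the more exposed part. The Discussion (Retention of participants) itself anticipates people withdrawing mid-session because they dislike the drink. Product-related withdrawal is what a limit on variation by arm is there to detect, and those are the records that the destruction rule reaches most clearly. Destroyed records cannot be recovered, so the matter has to be settled before the first withdrawal.

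**Working it through.** **1. The plan's own figure.** Sample size gives two-sided alpha 0.05, power 0.8, delta 0.3977 and SD 1 for a paired t test. The exact noncentral-t calculation gives n = 51.58, rounded up to 52 (power at 52 is 0.803). The stated 52 reproduces and is not in dispute. It serves below as the number of completers.

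**2. The rules side by side.**

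| Who leaves | Data collection methods | Deviant participants section | Data handling section |
|---|---|---|---|
| Tells the investigator they wish to stop | log as drop-out, by product session | if mid-session, collect nothing further | destroy everything |
| Removed for persistent breach (also called withdrawn) | log as drop-out | do not use the data | destroy everything, if removal counts as withdrawal |
| Does not return for session 2 | log as not completing | silent | unclear; may not count as withdrawal |

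The first row carries three instructions for one person. Collecting nothing further suggests that earlier data stay; destroying everything does not.

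**3. Where the 30% limit falls.** With drop-outs replaced until 52 complete, D drop-outs give attrition D/(52 + D). The limit is met when D ≤ 0.3 × 52/0.7 = 22.3.

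- D = 22: 22/74 = 29.7%, met.
- D = 23: 23/75 = 30.7%, breached.

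**4. Effect of erasure.** If w of the D drop-outs vanish from both counts, the measured rate is (D − w)/(52 + D − w). That is the rate of a trial with only D − w drop-outs. The criterion is therefore wrongly met once w reaches D − 22: one record if D = 23, eight if D = 30.

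Illustration with assumed counts (not in the documents): 82 consent and 30 do not complete.

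| Records erased | Measured attrition | 30% limit |
|---|---|---|
| 0 | 30/82 = 36.6% | breached |
| 5 | 25/77 = 32.5% | breached |
| 10 | 20/72 = 27.8% | met |
| 20 | 10/62 = 16.1% | met |
| 30 | 0/52 = 0% | met |

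**5. Split by arm.** Same assumed 82, taken as 41 starting on each product, with 20 and 10 drop-outs.

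- Nothing erased: 20/41 − 10/41 = 48.8% − 24.4% = 24.4 points.
- Half erased in each: 10/31 − 5/36 = 32.3% − 13.9% = 18.4 points.
- Ten erased in the first arm only: 10/31 − 10/41 = 32.3% − 24.4% = 7.9 points, now inside 10.
- All erased: 0 points.
- All 20 erased in the first arm only: 0% − 24.4% = −24.4 points, a reversal of sign.

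Each arm's rate can only fall. The difference usually shrinks, but uneven erasure can also reverse it.

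**The case against.** A reader might infer that the attrition criterion cannot be computed at all, that measured attrition would be 0%, or that the criterion would pass whatever happened. The documents do not support this. It would require every drop-out to be a formal withdrawal and every tally to be erased as well. Several points stand against it.

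- The plan explicitly orders drop-out logs. An anonymous tally need not be a participant's information, and if the logged counts are kept, nothing is lost.
- Trial withdrawal describes withdrawing as telling the investigator, or being removed for breaches. Someone who just fails to attend session 2 is not clearly covered by the destruction rule.
- Envelopes are numbered and taken in order, and the chief investigator generates a sequence for each venue. Numbers used minus numbers completed could recover overall attrition, and the list gives each missing participant's sequence and so the first-session product.
- Safety information is not confined to the participant's file. "Any adverse events that are reported to the PI will be logged using an adverse event form", and reports also go to the chief investigator and the ethics committee Chairperson. Un-blinding disclosures go to the chief investigator. Literal destruction makes no exception for the form, but a wholesale loss of safety data does not follow.
- This is a condensed article, and a fuller protocol may say exactly what is erased.

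These points limit the size of the problem without removing it. The article nowhere says that a tally survives, and reconstruction from envelopes is an unstated workaround that would not give the session or product at drop-out that the logs are meant to hold. Nor is this missing detail: the article prints two rules that conflict.

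**Conclusion.** The concern holds as a conflict between stated rules that bears on the primary outcome. If the destruction rule is applied literally to those who formally withdraw, attrition and its split by arm cannot be reliably computed. The overall rate, and the rate within each arm, are biased downwards and so towards meeting the 30% limit; the difference between arms becomes untrustworthy.

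The documents do not allow the size to be fixed, because it depends on what share of drop-outs are formal withdrawals and whether the logged counts are kept. It ranges from no effect (counts kept) to complete concealment (every drop-out a withdrawal, every count erased). Near the limit it takes little: with 52 completers, one lost record separates 23/75 = 30.7% from 22/74 = 29.7%. These figures assume replacement until 52 complete, and the figures by arm assume that drop-outs are classified by first-session product. The stated sample size is unaffected.

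**What to change.** Amend the sentence in Data handling, record keeping and retention. On withdrawal, identifiable information is destroyed, but a de-identified record of each consented, randomised participant is kept: study number, venue, sequence, session and product at drop-out, and any adverse event logged. Where a participant asks for erasure, keep at least an anonymous count by sequence and time of drop-out.

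State that all of these count in the numerator and denominator of the attrition criterion. Bring Trial withdrawal, Data collection methods and Collecting data from deviant participants into line with the new wording, and say whether non-attendance at session 2 and removal by the team count as withdrawal.

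Keeping the units drunk by withdrawn participants is optional; the criterion does not need them, and it would go further in changing what participants were promised.

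The cost is a small change to the withdrawal undertaking, which needs ethics committee approval. The participant information sheet and consent form are not shown; if they carry the same promise, they need the same change.
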